## Abstract

**Background:**

Treatment outcomes of HIV-positive individuals are threatened by low antiretroviral therapy (ART) adherence, a problem that is particularly acute among youth. Incentives are a promising tool to support ART adherence, but traditional incentive designs rewarding uniformly high levels of the desired health behavior may demotivate those with low levels of the behavior. In this study, we investigate the effectiveness of alternative approaches to target-setting for incentive eligibility using subgoals (i.e., individual-specific, interim targets leading up to the optimal target).

**Methods / design:**

We will enroll 628 HIV-positive youth between ages 15 and 30 into a 3-year randomized controlled trial. Participants will be randomized 1:1:1:1 to a control arm or one of three intervention arms (*n* = 157 each) that allow them to enter a prize drawing for small incentives if their ART adherence meets the given goal. In the first arm (T1, assigned subgoal), goals will be externally assigned and adapted to their initial adherence level. In the second arm (T2, participatory subgoal), participants can set their own interim goals. In the third arm (T3, fixed goal), all participants must reach the same target goal of 90% adherence. T1 and T2 participants are required to reach 90% adherence by month 12 to participate in a larger prize drawing. The control group receives the usual standard of care. All four groups will receive weekly motivational messages; the three treatment groups will additionally receive reminders of their upcoming prize drawing. Adherence will be measured continuously throughout the intervention period using electronic devices and for 12 months post-intervention. Surveys will be conducted at baseline and every 6 months. Viral loads will be measured annually. The primary outcome is Wisepill-measured adherence and a binary measure for whether the person took at least 90% of their pills. The secondary outcome is the log-transformed viral load as a continuous measure.

**Discussion:**

Our study is one of the first to apply insights about the psychology and behavioral economics of goal-setting to the design of incentives, by testing whether conditioning the eligibility threshold for incentives on subgoals (interim goals leading up to the ultimate, high goal) improves motivation and adherence more than setting a uniformly highly goal, and a comparison group.

**Trial registration:**

ClinicalTrials.gov NCT05378607. Date of registration: May 18, 2022.

**Supplementary Information:**

The online version contains supplementary material available at 10.1186/s13063-023-07449-z.

## Background

In Sub-Saharan Africa (SSA), 25.6 million people are living with HIV, accounting for 71% of the global total (WHO 2016). Achieving long-term health and reduced likelihood of transmission requires lifelong, high medication adherence, yet low adherence is prevalent among youth, both in the USA and abroad. A recently released U.S. study found only 12% of youth to be virally suppressed [1]. A longitudinal study from South Africa following youth and adults found that adolescents aged 11–19 were approximately 50% less likely than adults to maintain optimally high adherence and 70–75% less likely to be virologically suppressed[2]. In our study among Ugandans aged 15–22, mean ART adherence was 64%, and fewer than 30% were adherent at the clinically desirable rate of 90% or higher [3].

Effective interventions to improve adherence and clinical outcomes for this population are urgently needed, yet a 2018 systematic review found that while there is a sizeable body of evidence on adherence interventions for adults, “current evidence is both sparse and lacking in quality” for adolescents [4]. Another recent review paper [5] found only seven intervention studies targeting youth living with HIV (YLWH), most of which were based in the USA and were small-scale pilot studies with small sample sizes. Clearly, more evidence is needed on what works to improve adherence among youth living in sub-Saharan Africa.

A growing body of work [6, 7] has documented a positive impact of incentives to shift complex health behaviors such as cardiovascular disease prevention [8], sexual behavior [9], and HIV-related behaviors including medication adherence among adults [10], HIV/STI testing [11, 12], and male circumcision [13]. Incentives work by providing a short-term reward for an action that otherwise has only long-term benefits, offsetting “present bias,” or the tendency of many people to act on short-term temptations rather than long-term considerations [14]. They may therefore be particularly appropriate for adolescents who discount the future at higher rates than adults [15]. Recent advances in developmental cognitive neuroscience show that adolescents are more reward-sensitive than adults [16]; adolescents’ socio-emotional brain system associated with impulsivity and risk-taking behavior develops faster than their cognitive control system, with associated problems for self-regulation [17]. Adolescents have consequently been found to derive greater satisfaction from incentives than adults [18].

It remains an open question how best to deliver incentives to improve health behaviors. In existing interventions, incentives typically reward individuals for reaching a certain performance goal, commonly a high threshold set uniformly for all individuals, such as a physical activity milestone [19], adherence of 90% [10], or viral suppression [20]. However, people differ in their levels of baseline performance and capacity to improve their performance. Because traditional, high uniform goals do not reward marginal improvements, they consequently reward those with already healthy behaviors. Individuals who are far from such a high threshold must exert great effort to reach it—and yet any marginal improvements they make will not be rewarded, leading to demotivation. For behaviors which require repeated actions such as (daily) adherence, this structure can discourage effort over time, leading to no or only minimal improvement among those not capable of immediately reaching the high goal. In our own studies, adherence improvements were driven by those with already relatively high initial adherence of about 60–80%. Those with adherence below this level did not benefit from our incentive intervention that set the eligibility threshold at 90% mean adherence, and reported that failing to win the incentives caused demotivation [10]. Adolescents and young adults have the lowest levels of self-esteem of any age group [21] and are therefore particularly susceptible to demotivation. Redesigning incentives to enable those (youth) with low baseline adherence to reach their goals is thus of paramount importance.

New research on behavior change shows that breaking up goals into smaller increments may be the key to reconciling short-term behavior with long-term aspirations [22]. Behavioral economics (BE), and more specifically Prospect Theory, provides a framework to conceptualize goals as reference points [23, 24]. The closer an individual is or gets to a goal, the more motivated they are to achieve it. Conversely, someone far away experiences demotivation [25], resulting in inaction. This concept supports subgoaling, i.e., creating smaller interim goals working towards to the ultimate goal as a solution to overcome the starting problem. Subgoaling takes advantage of individuals working harder when their goal feels more attainable, reinforces motivation by rewarding marginal improvements [26, 27], and boosts task persistence [28]. The approach is most useful when people are doubtful about reaching or are performing far below a distant goal [29, 30].

Allowing participants to set their own interim goals increases agency / ownership [31] and in turn heightens self-efficacy, goal commitment, and performance, compared to assigned (i.e., externally assigned) goals [32–34]. It further avoids the concern that intrinsic motivation may be crowded out by external rewards [35]. This approach also leverages information the participant holds about their capability to reach a goal not evident to the interventionist, i.e., the participant’s private information.

In this study, Goals for Adherence with Low-cost Incentives (GOALS), we will test two approaches to setting interim goals to test the relative contribution of subgoaling and ownership. It is well established in the psychology literature that goals mediate the effect of incentives on performance [36]. Yet evidence is lacking in terms of how to best set the eligibility goals in incentive interventions. GOALS proposes testing externally assigned subgoals (first treatment arm) and participatory subgoals (second treatment arm) with the goal to reach at least 90% adherence. The objective in year 1 is to identify the incentive design most effective for improving adherence. In addition to these interim prize drawings at regular clinic visits, there will be a larger prize drawing at month 12 to make achieving the 90% goal particularly salient. All treatment arms will receive weekly SMS motivational reminders with the goal of keeping incentives and their associated goals at the top of participants’ mind in the weeks between clinic visits. In year 2, the objective is to maintain adherence improvements and achieve viral suppression. Therefore, during the maintenance phase, incentive group participants will be required to remain 90% adherence, with a larger prize drawing for achieving viral suppression at the end of the maintenance phase. Most incentive studies measure behavior change over the short term (less than 6 months) [6]. By explicitly designing incentives to address the dual goals of improvement (year 1) and maintenance (year 2), we provide much-needed evidence on how to sustain adherence over time and prevent performance backsliding. GOALS will measure adherence for 6 months after the intervention ends to assess the impact of the different treatment arms on behavior change once incentives are withdrawn (persistence).

## Methods

### Study design

The study is a parallel group randomized controlled trial, designed as a superiority trial with the primary goal of evaluating whether the GOALS intervention implemented alongside standard care is superior to the standard care alone provided at the Mildmay hospital. Randomization will be performed as block randomization with a 1:1:1:1 allocation. We will recruit participants and monitor their ART adherence using Wisepill devices to measure pill container openings remotely for 3 months. After this period (henceforth “observation period”), we will identify clients exhibiting low adherence, the target population for our intervention. All clients who adhere to less than 90% of their medication in the month before their baseline visit will be recruited for the intervention phase, and randomly assigned to one the GOALS study arms, and those with adherence higher than 90% will be unenrolled.

We will randomize these participants with low adherence into one of four equal-sized study arms for the first year of the intervention (“*Improvement phase*”). In the three treatment arms, participants will be eligible for a prize drawing to win small amounts of mobile airtime of either 500, 5000, or 10,000 Ugandan Shillings (approximately $0.15, $1.50, and $3, respectively) if they reach the adherence goal required in the respective treatment arm. Those randomized to the fourth group will receive usual care as well as weekly text messages, but no incentives. The goals will be set as follows for the different study arms:Assigned subgoals (T1): in this group, the study coordinator will choose the ART adherence target for the participant. This will be done as follows: given an expected four prize drawings during the first year of the intervention, the study coordinator will measure the participant’s baseline adherence and gradually increase the target every 3 months by equal amounts, working towards 90% adherence at the end of year 1. For example, for someone with 50% baseline adherence, the study coordinator would calculate (90% − 50% = 40%; 40%/4 = 10%), and set the adherence targets at the four study visits equal to 60% at month 3, 70% at month 6, 80% at month 9, and 90% at month 12.Participatory subgoals (T2): the participant will choose their own adherence target every 3 months, working towards 90% adherence at the end of year 1. Each target chosen must be higher than the highest adherence ever achieved. For example, someone selected their adherence target in 3 months to be 70%, but they actually achieve 75%. The next target they choose must then be 75% or higher. If a given target was not achieved, the participant can then choose one that is equal or higher to the one chosen previously.Fixed goal (T3): the study participant must reach a fixed (i.e., non-varying) target adherence level of 90% at each study visit; this arm corresponds to how adherence interventions typically are implemented.Control group (T4): will receive the usual standard of care offered at Mildmay Uganda.

The three treatment groups will receive weekly motivational messages and a reminder of their upcoming prize drawing. Weekly SMS messages will help maintain contact with study participants and enable them to become accustomed to receiving messages from the study for potential remote prize drawings (given the evolving COVID situation and corresponding clinic changes towards visits that are more spaced out, we expect some prize drawings to be done in person, and others remotely as further detailed below). In contrast, the control group will only receive the motivational portion of the text messages (without the reminders of the possibility of winning prizes) as an attention control due to the potential beneficial effects of text messages.

After the first year of the study, we will evaluate participants in the treatment groups to determine those who achieved high adherence of at least 90% (high adherers) and those who did not (low adherers).

Figure 1 below shows that in year 2, high adherers will progress to the “Maintenance phase” between months 12 and 24 where we will assess the intervention’s effectiveness in maintaining at least 90% adherence. They will have the chance to win prizes every 3 months if they maintain their adherence at or above 90% throughout this phase. They will then move to the “Persistence phase” between months 25 and 36 to assess the treatment arms’ impact on long-term adherence once incentives are removed.

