#### Exclusion criteria

Exclusion criteria for the 3-month observation period preceding the GOALS intervention and for the GOALS intervention:Is not willing or able to use the Wisepill device when taking ART medicationHas mental health problems that require immediate treatment (e.g., psychotic symptoms), a diagnosed mental disorder that would limit the ability to participate (e.g., dementia), or cognitive impairments that result in a limited ability to provide informed consent.No longer has access to a phone (less than 5 out of 7 days), if phone access changed over the course of the 3-month observation periodParticipating in another studyUnable to read

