#### Quarterly prize drawings

Participants in the three treatment arms will be eligible to enter an in-person or remote prize drawing for a mobile airtime reward every 3 months if they meet their target adherence. In-person prize drawings will be done if the date of the drawing coincides with the participants’ regularly scheduled clinic visits; otherwise, they will be done remotely. Wisepill records adherence remotely, so the study team can monitor adherence without an in-person visit. Remote prize drawings will be conducted automatically by the computer, and the results and airtime reward texted to the participant over the phone.

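### The inclusion criterion for phone access is printed with the same threshold and direction as the exclusion for losing access, so the two contradict each other

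*Protocol article*

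**What the plan says.** The Inclusion criteria section of the protocol article lists three requirements for entering the 3-month observation period. The third is regular access to a mobile phone, with a bracket that sets this at fewer than 5 days in 7.

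The Exclusion criteria section, which covers both the observation period and the intervention, repeats the bracket for the loss of access: "No longer has access to a phone (less than 5 out of 7 days), if phone access changed". The condition at the end of that sentence limits it to changes during the 3-month observation period.

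Elsewhere the article describes how far the trial depends on the phone:

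- Background: "All treatment arms will receive weekly SMS motivational reminders".
- Study design: "Weekly SMS messages will help maintain contact with study participants and enable them to become accustomed to receiving messages from the study". As an attention control, "the control group will only receive the motivational portion of the text messages". Rewards are mobile airtime.
- Quarterly prize drawings: "Remote prize drawings will be conducted automatically by the computer, and the results and airtime reward texted to the participant over the phone". Not every drawing is remote: "In-person prize drawings will be done if the date of the drawing coincides with" a regular clinic visit.

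No other section gives a phone-access threshold.

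**The concern.** One threshold in one direction cannot define both having access and having lost it. The inclusion side is the one that clashes with its own wording, because access on fewer than 5 days in 7 is not what regular access would ordinarily mean. It also clashes with an intervention that uses weekly texts, prize reminders, remote drawings and airtime.

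If screening followed the bracket, clients with the best phone access would be turned away and some with limited access enrolled. That could reduce how much of the intervention is received, and the enrolled group would differ from the one the design describes. If screening did not follow it, the published rule misdescribes who was enrolled, and anyone replicating or applying the trial would work from a wrong criterion. The text needs correcting in either case.

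**Working it through.** No sample size, power or alpha figure enters this point. The check sets the two criteria side by side, treating access as days per week from 0 to 7.

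**Step 1: apply the inclusion bracket literally.** Fewer than 5 days means 4 or less. Access on 5, 6 or 7 days fails the bracket.

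**Step 2: apply the exclusion.** It removes people below 5 days only if their access changed during observation.

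**Step 3: compare the printed bracket with its complement.**

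| Client's phone access | Inclusion bracket as printed | Inclusion bracket as at least 5 of 7 days |
|---|---|---|
| Stable, 5 to 7 days | Not admitted | Admitted and kept |
| Stable, below 5 days | Meets the bracket; not removed by the exclusion | Not admitted |
| 5 to 7 days at recruitment, falling below 5 during observation | Not admitted, so the exclusion never arises | Admitted, then excluded |

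The third row shows which way the error runs. An exclusion for no longer having access presupposes people who once had it. With the bracket as printed, anyone who could fall from 5 or more days to below 5 has already been refused, so the exclusion loses its evident purpose. With the inequality reversed, the two criteria fit together: admit at 5 to 7 days, and exclude on a fall to below 5.

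**Step 4: look for a passage that resolves the conflict.** None does. The sections on Study design, Quarterly prize drawings, Recruitment, and Baseline survey and randomization show reliance on the phone or describe enrolment, but none restates the threshold.

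**Step 5: check whether the planned numbers depend on it.** Sampling and participants builds the targets as 4 × 140 = 560; 560 × 1.06² = 560 × 1.1236 ≈ 629, reduced to 628 for equal arms; and 628 / 0.50 = 1256. The 50% is the share expected to be eligible on adherence. Phone access is not an input, so these targets do not move.

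**Step 6: check comparability of the arms.** Both criteria act before randomisation and apply alike to all four arms. A wrong threshold would change who enters the trial, not how the arms compare at baseline.

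**The case against.** The strongest reply is that this is a slip of wording whose intended meaning is plain. The main clause asks for regular access, and the exclusion treats fewer than 5 days as no access. Nothing suggests that screening staff turned away clients with daily phone access. That reply stands as to intent. It does not remove the contradiction from a printed eligibility rule.

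A reader might go further and infer that the trial selects the people least able to receive the intervention, or that everyone with access on 0 to 4 days passes. The document does not support either inference. The second keeps the bracket and discards the main clause: a person with no phone access at all does not have regular access. The first treats a probable drafting error as a selection strategy.

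A reader might also infer that participants will often miss messages and that differences from control will shrink. That is not shown:

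- Messages are weekly and drawings quarterly, so access on 3 or 4 days a week need not prevent receipt.
- Strategies to improve adherence to intervention protocols says that sending success is tracked weekly and failed messages are resent. This shows sending, not reading, but it is a safeguard.
- Some drawings take place in person.
- Data management says that the Wisepill device transmits through its own SIM card, so adherence measurement does not depend on the participant's phone.

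Finally, this is a condensed article. The full protocol and the screening forms are not shown, so what was applied in practice cannot be judged from it.

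**Conclusion.** The contradiction is real and sits in the Inclusion criteria set against the Exclusion criteria. The Study design sentences about text messages are sound and only show why phone access matters. Reading the bracket as a reversed inequality is an inference, though a strong one, from the words around it and from the purpose of the exclusion.

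The demonstrated size is one wrong eligibility threshold in the Methods. The article gives no distribution of phone access, so the share of clients affected cannot be computed. Sample size, power and comparability of the arms are untouched. Weaker delivery or narrower generalisability would follow only if screeners applied the bracket as printed. The document gives no sign that they did, and none that they did not.

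It is worth settling now. Trial status gives a study start of 25 April 2022 and a protocol date of 5 May 2023, with recruitment under way.

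**What to change.** 1. In the Inclusion criteria, define regular phone access as at least 5 of 7 days, so that it complements the exclusion.
2. Confirm which threshold and direction the actual screening form uses, and has used since recruitment began. The article does not say that phone-access screening is done in SurveyCTO, so the check should cover whatever form or tool staff used.
3. Only if the printed wording was applied at any point, report by arm the number enrolled with access below 5 days.

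The cost is a correction of a few words and one check of the screening form. The tabulation by arm arises only if that check shows a problem. No change to the design, the sample size or the analysis is needed.

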**Fig. 1 Fig1:**
[figure not shown]
Table showing different phases of the participants in different groups throughout the study

Low adherers will be given an additional 6 months in the “Improvement phase” between months 12 and 18. During this time, low adherers in the participatory subgoals group will have one more opportunity to set their personal target; they will be encouraged to set a target at month 15 such that they would achieve 90% by month 18. Low adherers in the assigned subgoals group will receive two more pre-chosen targets starting from their adherence at month 12 in equal increments up to 90% (e.g., if month 12 adherence is 80, their target is 85 for month 15 and 90 for month 18). The maintenance phase for the low adherers in the assigned goal and participatory goal groups will begin at month 18 for 12 months.

Low adherers in the fixed goal group will maintain their target of 90%. At month 18, we will identify the treatment arm with the highest effectiveness and move low adherence participants in the fixed goal arm to that arm to give them an opportunity to also benefit from the intervention. These participants will continue in the improvement phase between months 18 and 30, while assigned subgoals and participatory subgoals participants move to the maintenance phase. Low adherers across in the participatory and assigned goals group will complete their “Persistence phase” of the study in months 30–36.

All participants in the treatment groups will be eligible for a larger prize drawing at the end of their maintenance phase if they achieve viral suppression, defined as a viral load of 200 copies/mL or less.

Follow-up surveys will be conducted every 6 months for 24 months, and a cost-effectiveness analysis will also be performed after 36 months to help determine the intervention design’s potential for sustainability and scale-up.

